### Exclusion criteria

Patients will be excluded if they:Have complications with serious heart failure (New York Heart Association class IV)Have severe and uncontrolled high blood pressure (systolic blood pressure ≥ 180 mmHg or diastolic blood pressure ≥ 110 mmHg)Have severe cardiopulmonary dysfunction, or serious primary disease of the liver, kidney, and hemopoietic system, or psychosis, or a malignant tumorHave a high risk of bleeding, such as a hemorrhage history of vital organs (brain or upper gastrointestinal tract) within the past 6 months, low platelet counts, coagulation disorder, or current treatment with warfarin or other anticoagulant therapyAre allergic to the study drugs (GXNT or aspirin) or its componentsAre pregnant, planning to be pregnant or breast-feedingHave previously been involved in another clinical trial in the past one month

### Settings and recruitment

Qualified drug clinical trial institutions or tertiary hospitals across mainland China have been invited, and the first 36 hospitals to agree to participate will be included. Each hospital is expected to recruit 100 eligible patients. Patients can be recruited by screening inpatients and outpatients of each hospital, through media advertising and social media or by screening a PCI database. Potential eligible patients will be screened and assessed by trained investigators, and eligible participants will be asked to provide written informed consent.

### Allocation

Thirty-six participating hospitals (clusters) with 3600 patients are firstly stratified by type of medication delivery (Western medical or traditional Chinese medicine hospitals), and then hospitals in each stratification are randomly allocated in a 2:1 ratio by a computer-generated, centrally controlled randomization schedule to treatment (24 hospitals with 2400 patients) or control (12 hospitals with 1200 patients) arms (see Fig. 1). All patients from one cluster will receive same intervention. Though the patients and caregivers are not blinded, the outcome assessors and data analysts are to be blinded to treatment allocation to minimize potential bias.

**Fig. 1 Fig1:**
[figure not shown]
Study flow chart. GXNT, Guanxinning tablet

### Interventions

All recruited patients will continue to receive aspirin (100 mg once daily) and other conventional treatment including lipid-reducing, antihypertensive, or antidiabetic therapy [23]. Patients recruited from hospitals in the treatment arm will additionally receive GXNT (0.38 g/tablet, China State Food and Drug Administration approval number Z20150028) four tablets each time, three times daily for the first 6 months, and reduce to four tablets each time, twice daily for another 6 months, whereas patients from the controlled hospitals will only receive conventional treatment. At 12 months, patients in the treatment arm will stop GXNT treatment, and then all participants in both the treatment and control arm will continue aspirin monotherapy and other conventional treatment for another 12 months, until month 24. Any kind of other traditional Chinese medicine, including Guanxinning injection, is not allowed for all participants during the whole trial period.

### Outcome measures

The primary efficacy outcome measure is the composite cumulative incidence of MACE, including cardiovascular death, non-fatal myocardial infarction, stent thrombosis, revascularization, ischemic stroke, and re-admission for unstable angina during the treatment and follow-up periods. The secondary efficacy outcome measures are stopping or reducing the rate of nitroglycerin tablets and the respective cumulative incidence of all-cause death, cardiovascular death, non-fatal myocardial infarction, stent thrombosis, revascularization, ischemic stroke, and re-admission for unstable angina. Other efficacy outcomes include hypersensitivity C-reactive protein and platelet aggregation rate. Patients’ costs, the Seattle Angina Questionnaire rating, and health-related quality of life determined by the generic Short Form-36 (SF-36) questionnaire will be additionally assessed for cost-effectiveness analysis.

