**Methods:**

We will conduct a cluster randomized controlled trial in 3600 eligible post-PCI patients from 36 tertiary hospitals (100 patients per hospital) across mainland China. The hospitals served as clusters are randomized in a 2:1 ratio to Guanxinning tablet (GXNT) plus aspirin or aspirin alone for 12 months, with other conventional treatment applied in both groups. After the treatment period, all patients will be followed up for another 12 months. The primary outcome measure is composite cardiovascular events including cardiovascular death, non-fatal myocardial infarction, stent thrombosis, revascularization, ischemic stroke, and re-admission due to unstable angina. Secondary outcome measures are all-cause mortality, each individual component of the primary outcome measure, and stopping or reducing the rate of nitroglycerin administration. Adverse events, including bleeding, will be closely monitored during the whole trial period. In addition, a cost-effectiveness study of GXNT for the study population will be conducted along with this trial.

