### Follow-up

After baseline visit, all participants will receive follow-up visits at 1, 3, 6, 9, 12, and 24 months, as scheduled (see Fig. 2 for SPIRIT figure). The primary and secondary outcome measures will be monitored during the whole study period. Most laboratory tests in the treatment arm will be tested at baseline and at 1, 3, 6, and 12 months, while in the control arm most tests will only be conducted at baseline. Platelet aggregation rate and hypersensitivity C-reactive protein level will be measured in both the treatment and control arm at baseline and in the third month in one or two selected centers in Shanghai to explore the potential effects of GXNT on platelet aggregation and inflammation.

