### Sample size and data analysis

As little data on MACE rate in post-PCI patients who switch from DAPT to aspirin for about 12 months is available, we have to calculate the sample size according to the results of other studies. One registry trial reported that the annual rate of death or myocardial infarction was approximately 4.7%/year for patients who underwent successful implantation of at least one drug-eluting stent and did not received prolonged DAPT [25]. Another retrospective study indicated that the 2 year composite rate of mortality, reinfarction, and target vessel revascularization for patients undergoing primary PCI after acute myocardial infarction was 23% to 30% [26]. Though participants in our trial may have a lower rate of mortality, reinfarction, and target vessel revascularization than the retrospective study, taking other components into account, including stent thrombosis, ischemic stroke, and re-admission for unstable angina, we estimate the 12 month rate for the primary outcome measure in patients taking aspirin alone might be 21%, and that GXNT will reduce the incidence by 21%. A statistic power of 0.8 and a type I error rate of 0.05 (alpha) are chosen. According to a previous study, we assume the coefficient of intracluster correlation to be 0.002 [27] and we expect to recruit 90 patients from each cluster (hospital). Thus, a total of 3240 patients with 36 clusters (hospitals) will be needed. Considering a dropout rate of 10%, a minimum of 3564 patients is needed; for convenience of randomization, we decided to recruit 3600 patients (100 patients per hospital) and 36 hospitals (2400 patients and 24 clusters in the treatment arm, 1200 patients and 12 clusters in the control arm). Considering the uncertainty of the MACE rates in the study population, an interim analysis will be conducted when one-third of expected MACEs occur and the sample size will be adjusted according to the results of the interim analysis.

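### The sample size and 80% power are derived for a 12-month event rate, but the primary outcome runs to 24 months with GXNT stopped at month 12

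*Protocol article*

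**What the plan says.** All references are to the protocol article.

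- **Outcome measures:** the primary outcome is the cumulative incidence of a MACE composite whose listing ends with "re-admission for unstable angina during the treatment and follow-up periods".
- **Abstract, Methods:** treatment lasts 12 months, and "After the treatment period, all patients will be followed up for another 12 months".
- **Interventions:** "At 12 months, patients in the treatment arm will stop GXNT treatment"; participants in both arms then "will continue aspirin monotherapy and other conventional treatment for another 12 months, until month 24".
- **Follow-up:** "The primary and secondary outcome measures will be monitored during the whole study period", with the last visit at month 24.
- **Sample size and data analysis:** "we estimate the 12 month rate for the primary outcome measure in patients taking aspirin alone might be 21" per cent, and "GXNT will reduce the incidence by 21" per cent. With power 0.8, alpha 0.05, an intracluster correlation of 0.002 and 90 patients per hospital, the section arrives at 3240 patients in 36 hospitals. It also plans an interim analysis once a third of the expected MACEs have occurred, with adjustment of the sample size.

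No section gives a 24-month control rate, an assumed GXNT effect after month 12, or a 12-month primary time point.

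**The concern.** The outcome definition and the sample size section describe different quantities. One covers months 0 to 24; the other covers 12 months, the same length as the GXNT course. In months 12 to 24 both arms receive the same care. Events in that year add to the count in both arms. Unless the benefit outlasts the drug, they also shrink the relative reduction.

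Two things are at stake. First, the power of the primary test is not stated anywhere, because the 80% belongs to another contrast. Second, if the horizon is settled only after data are seen, the choice between a 12-month and a 24-month result is open to challenge.

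The ambiguity also reaches the interim analysis, since the number of expected MACEs depends on the horizon. Under Data management and monitoring, that interim look can end the trial early if it shows no trend of benefit.

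**Working it through.** **Inputs from Sample size and data analysis.** Control rate p₁ = 0.21. GXNT rate p₂ = 0.21 × 0.79 = 0.1659, a difference of 0.0441. Power 0.80; intracluster correlation 0.002; 90 patients per cluster; 2:1 allocation. Data analysis in the same section specifies two-sided 5% tests.

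**Step 1: reproduce the article's figure.** Pooled-variance formula for two proportions, no continuity correction:

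n(control) = [1.960·√(1.5·p̄(1−p̄)) + 0.842·√(p₁(1−p₁) + p₂(1−p₂)/2)]² / (p₁−p₂)²

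with p̄ = (0.21 + 2 × 0.1659)/3 = 0.1806.

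- n(control) = (0.9234 + 0.4081)² / 0.0441² = 911.6, rounded up to 912; total 3 × 912 = 2736.
- Design effect = 1 + 89 × 0.002 = 1.178; 2736 × 1.178 = 3223.
- Control clusters: 912 × 1.178 / 90 = 11.94, rounded to 12; with 24 on GXNT that is 36 clusters, or 3240 patients.

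Power at 3240, with effective sizes 1080/1.178 = 916.8 and 2160/1.178 = 1833.6: the standard error is 0.01556 under the null and 0.01601 under the alternative. Power = Φ((0.0441 − 1.960 × 0.01556)/0.01601) = 80.2%.

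So 3240 and 80% are the figures for 21% versus 16.59% at 12 months.

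**Step 2: carry the same assumptions to month 24.** The article supplies neither of the two quantities needed, so both are assumed:

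- r, the second-year control risk among patients event-free at month 12, from 5% to 21% (21% repeats the first-year risk);
- f, the second-year risk ratio for GXNT: 1 if the effect ends with the drug, 0.895 if half the 21% reduction persists, 0.79 if all of it persists.

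Control 24-month risk = 1 − 0.79(1 − r). GXNT 24-month risk = 1 − 0.8341(1 − r·f). Power is computed as in Step 1 with the same effective sizes.

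| r | Control, 24 m | GXNT, 24 m (f = 1) | Relative reduction (f = 1) | Power, effect ends | Power, half persists | Power, all persists |
|---|---|---|---|---|---|---|
| 5% | 25.0% | 20.8% | 16.8% | 70.0% | 78.5% | 85.5% |
| 10% | 28.9% | 24.9% | 13.7% | 60.5% | 77.9% | 89.9% |
| 15% | 32.9% | 29.1% | 11.4% | 52.2% | 78.0% | 93.3% |
| 21% | 37.6% | 34.1% | 9.3% | 43.8% | 79.1% | 96.3% |

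Worked cell (r = 21%, f = 1): difference 0.3759 − 0.3411 = 0.0348; standard errors 0.01933 and 0.01945; Φ((0.0348 − 1.960 × 0.01933)/0.01945) = 43.8%.

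Evaluable patients needed for 80% power if the effect ends with the drug, by the Step 1 formula: about 4140, 5160, 6300 and 7860 for the four values of r. If half persists: about 3320 to 3420.

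**Step 3: the interim trigger.** Expected events in 3240 patients at 12 months: 1080 × 0.21 + 2160 × 0.1659 = 585, a third being 195. At 24 months with r = 21% and f = 1: 1080 × 0.3759 + 2160 × 0.3411 = 1143, a third being 381.

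**The case against.** **A 24-month outcome is a legitimate choice.** The Background states an interest in long-term benefit, and asking whether a 12-month course leaves patients better off at two years is a proper intention-to-treat question. This stands. Nothing in the article shows that 12 months is the right time point; the fault is that the sizing does not match the outcome chosen.

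**The direction of the error is not known.** This also stands. A reader might infer that the trial is underpowered, or that power is about half of what is claimed. The documents do not support that without conditions. The 44% figure needs both no persisting effect and a second-year risk as high as the first. With full persistence, power exceeds 80% throughout the range examined.

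**The interim adjustment already deals with uncertain rates.** In part. The article acknowledges uncertainty in the MACE rate and plans to adjust the sample size. It names neither the horizon nor an effect after GXNT stops, and the trigger itself depends on the horizon (Step 3).

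**An article condenses the full protocol.** True, but both windows are printed here, and they differ. An analysis plan could specify the analysis in more detail; it would not turn a 12-month calculation into a 24-month one.

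**A further inference to avoid.** The article cites a study in which the "2 year composite rate of mortality, reinfarction, and target vessel revascularization for patients undergoing primary PCI after acute myocardial infarction was 23% to 30" per cent, and a reader might conclude that 21% was really a two-year rate. That source counts three components. The article says its 21% allows for further ones: stent thrombosis, ischemic stroke and re-admission for unstable angina. The two rates are not like for like, and this point does not rest on comparing them.

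**Conclusion.** The point holds in this form: the 80% power is correct for a 12-month comparison of 21% with 16.59%, and it is not the power of the 24-month primary outcome that the article defines. How far the true power departs from 80% cannot be settled from the article. Under the assumptions above it lies between about 44% and 96%. It stays just below 80% when half the effect persists, so reaching 80% would need somewhat more than half of the reduction to continue off drug, an assumption that the article neither states nor supports.

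These figures rest on the article's own 21% rate, 21% reduction and intracluster correlation of 0.002, with 3240 patients analysed at both horizons, and on the assumed second-year risks of 5% to 21%. Because the mismatch concerns the primary outcome and its power, it should be resolved before any outcome data are compared by arm.

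**What to change.** Reconcile Outcome measures with Sample size and data analysis in one of two ways.

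1. **Keep 24 months as primary.** State the 24-month control rate, the assumed GXNT effect after month 12 and the resulting power, preferably over a range of both assumptions.
2. **Make month 12 the primary time point**, with 24-month cumulative MACE as a secondary outcome. The stated 80% then applies, on the article's own assumptions.

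The choice depends on the question the sponsor wants answered; either is defensible. In both cases, state the horizon used to count expected MACEs for the interim analysis.

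**Cost.** A protocol amendment and matching registry wording; no extra visits, since follow-up to month 24 is already planned. The second option needs no extra patients but changes the primary question. The first may oblige the sponsor to report power below 80%. Restoring 80% by recruitment would take about 4140 to 7860 evaluable patients if no effect is assumed after GXNT stops, and about 3320 to 3420 if half is assumed to persist, both before allowance for dropout.

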### Safety outcomes and compliance monitoring

The incidence of bleeding defined according to the Bleeding Academic Research Consortium definitions [24], any adverse events or serious adverse events, and compliance of the participants will be closely monitored and recorded during the whole trial period. If necessary, treatment will be ceased and patients will be withdrawn according to the nature of adverse events or serious adverse events. Compliance of the participants with the intervention is assessed by counting tablets of GXNT and reviewing tablet log records.

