Data analysis will be conducted by Nanjing Medical University. All analyses will be performed on the individual level with adjustment for clustering and all available data from the dropouts will be included in the analysis up to the time of dropout where possible. All statistical hypothesis tests will be two-tailed and performed at a 5% significance level. Continuous variables will be presented as means and standard deviation, median or interquartile range. Categorical variables will be expressed as frequencies and percentages. Normality of relevant data will be examined using the Shapiro–Wilk test. Cluster-adjusted baseline differences between arms will be analyzed using the independent Student’s *t* test or the Mann–Whitney test for continuous variables and the Pearson *χ*^2^ test for categorical variables. All outcome measures, including the primary outcome measure, will be analyzed using a generalized linear mixed-effect model with the fixed effect being the intervention and the random effect being hospitals, to account for the potential correlation of outcomes within each hospital. Moreover, we will calculate the absolute rate reduction with 95% confidence interval as a crude estimate of the rate difference between the treatment and control groups by using the Mantel–Haenszel method. The number needed to treat for the primary outcome measure as the inverted absolute rate reduction will also be calculated. Efficacy outcomes are to be analyzed according to the intention-to-treat principle.

Safety outcomes will be assessed among all randomized patients except those who do not take any study medication or who have no safety records. The safety outcomes will be summarized and analyzed using the approach outlined.

Missing data will be accounted for by the modern imputation methods and all analysis will be conducted using SAS software version 9.4 (SAS Institute, Cary, NC, USA).

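### The adverse-event rule joins stopping treatment to withdrawing the patient, against intention-to-treat and outcome monitoring to month 24, so later events may go uncollected

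*Protocol article*

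**What the plan says.** All places are in the Methods of the protocol article.

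- **Safety outcomes and compliance monitoring:** if necessary, "treatment will be ceased and patients will be withdrawn according to the nature of adverse events or serious adverse events". The section does not say whether the withdrawal is from treatment or from the study.
- **Follow-up:** "all participants will receive follow-up visits at 1, 3, 6, 9, 12, and 24 months", and "The primary and secondary outcome measures will be monitored during the whole study period".
- **Outcome measures:** "The primary efficacy outcome measure is the composite cumulative incidence of MACE", counted over both the treatment and the follow-up periods, so to month 24.
- **Sample size and data analysis:** "Efficacy outcomes are to be analyzed according to the intention-to-treat principle". For dropouts, "all available data from the dropouts will be included in the analysis up to the time of dropout where possible". Also, "Missing data will be accounted for by the modern imputation methods". All outcomes are analysed with a "generalized linear mixed-effect model with the fixed effect being the intervention and the random effect being hospitals". The article states no distribution, link, censoring rule or person-time offset. Dropout is set at 10% overall and is not split by arm.

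**The concern.** Intention-to-treat needs outcomes on every randomised patient, whether or not treatment continues. A site that reads the adverse-event rule literally would stop treatment, take the patient out of the trial and record no later MACE or bleeding. Events that were never collected cannot be recovered at the analysis stage.

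Such a loss need not be balanced. Only GXNT hospitals give an added drug that can be stopped. Patients and caregivers know the allocation. Most laboratory tests are repeated at months 1, 3, 6 and 12 in the GXNT arm, but are done only at baseline in the control arm, so abnormal findings are more likely to surface on GXNT. Patients stopped for adverse events may also differ in prognosis. The treatment comparison could then be distorted by who was followed.

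A second, linked matter is how a withdrawn patient enters the primary analysis. The promise to use data up to dropout is met only by a model that carries follow-up time, and none is stated.

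**Working it through.** **1. The passages side by side.** The safety section names two acts, ceasing treatment and withdrawing the patient. If withdrawal meant only coming off treatment, the second act would repeat the first, so leaving the trial is the natural reading. The Follow-up section covers all participants to month 24, and the analysis section promises intention-to-treat. No sentence says that a patient who stops for an adverse event stays in outcome follow-up. The texts need reconciling.

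**2. The plan's own figure.** Control risk is 21% at 12 months. A 21% reduction, read as relative, gives 0.21 × 0.79 = 16.59% on GXNT, a difference of 4.41 points. With two-sided 5%, power 0.80, 2:1 allocation and pooled variance, the two-proportion formula gives 912 control patients and 2736 in all. The design effect is 1 + 89 × 0.002 = 1.178, and 2736 × 1.178 = 3223. That is 912 × 1.178 / 90 = 11.94 control hospitals, rounded to 12, so 36 × 90 = 3240 as stated. A 10% loss is covered: 3240 / 0.9 = 3600. The issue is possible bias, not power.

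**3. Illustration A: dropouts counted as event-free.** Assumptions: no true effect, constant hazard, exits uniform over the period, and arm splits chosen so that the total is 10%: (2 × 13 + 4)/3 = 10 and (2 × 12 + 6)/3 = 10.

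- Hazard: h = −ln(0.79) = 0.2357 per year.
- Mean observed risk in a dropout: 1 − 0.21/0.2357 = 0.1091.
- Observed arm risk at dropout d: (1 − d) × 0.21 + d × 0.1091 = 0.21 − 0.1009d.

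| Split, GXNT/control | GXNT | Control | Risk ratio |
|---|---|---|---|
| 13% / 4% | 0.1969 | 0.2060 | 0.956 |
| 12% / 6% | 0.1979 | 0.2039 | 0.970 |
| 10% / 10% | 0.1999 | 0.1999 | 1.000 |

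The 13%/4% row is a spurious relative reduction of 4.4%, about one fifth of the planned 21%. Equal dropout gives none.

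The primary outcome runs to month 24. If the same hazard held throughout, the risk would be 1 − 0.79² = 0.3759 and the mean observed risk in a dropout 1 − 0.3759/0.4714 = 0.2027. The observed risks are then 0.3534 and 0.3690 (ratio 0.958), or 0.3551 and 0.3655 (ratio 0.972).

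**4. Illustration B: the handling rule changes the sign.** Assume that an excess w of GXNT patients is withdrawn at month 3, none in control, with no true effect before withdrawal. Risk by month 3 is 1 − exp(−0.2357/4) = 0.0572. For w = 10% at 12 months:

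- *Counted event-free, later risk unchanged:* 0.9 × 0.21 + 0.1 × 0.0572 = 0.1947, which is 1.5 points below 0.21.
- *Event-free withdrawals dropped, later risk unchanged:* 0.1947 / (0.9 + 0.1 × 0.0572) = 0.2150, which is 0.5 points too high and so against GXNT.
- *Event-free withdrawals dropped, later risk doubled:* the full-follow-up risk is 0.9 × 0.21 + 0.1 × 0.338 = 0.2228. The observed 0.2150 is 0.8 points too low and so in favour of GXNT.

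Range in points for w from 1% to 10% (minus favours GXNT):

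| Rule | 12 months | 24 months |
|---|---|---|
| Counted event-free, risk unchanged | −0.15 to −1.5 | −0.3 to −3.2 |
| Dropped, risk unchanged | +0.05 to +0.5 | +0.04 to +0.4 |
| Dropped, risk doubled | −0.08 to −0.8 | −0.2 to −1.7 |

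For scale, the planned 12-month effect is 4.41 points.

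**The case against.** The strongest reply is that withdrawal may mean withdrawal from treatment. The rule is conditional and case by case, and read with the Follow-up section and the intention-to-treat statement it need not remove anyone from observation. That stands as a possible reading. It does not remove the problem, because a site needs one instruction and the text supports two.

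Three stronger readings are tempting, and the article does not support them.

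- **That the primary model cannot use partial follow-up.** The cumulative incidence, the two-proportion sample size, the Mantel–Haenszel rate difference and the number needed to treat all suggest one yes/no outcome per patient. But the article never calls the model binary. A Poisson mixed model with a person-time offset, or a model over visit intervals, belongs to the same class and uses time to dropout. Such detail is commonly left to an analysis plan.
- **That dropouts will be counted as event-free, or that the two missing-data statements contradict each other.** Event-free counting is stated nowhere. Using observed data where possible and imputing the rest can be complementary.
- **That outcomes are lost mainly on GXNT and imitate a benefit.** The rule is not limited to one arm, both arms take aspirin, bleeding could lead to stopping in either, and the 10% dropout is not split. The Background even reports no adverse events in daily use of GXNT. Unequal loss is plausible from the design, but the 13%/4% split is an assumption.

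**Conclusion.** The point holds as an unreconciled rule with a risk of bias. On its natural reading, the adverse-event sentence ends outcome collection for patients stopped for adverse events, against intention-to-treat and against monitoring of all participants to month 24. The comparison may be biased; the article does not show that it will be.

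Size and direction depend on the arm split and on the handling rule, and the article gives neither. The risk ratios 0.956 and 0.970 rest on assumed splits, uniform exits, a constant hazard and event-free counting, and they refer to 12 months, whereas the primary outcome runs to month 24. They show that an imbalance within the planned 10% dropout could matter. They are not estimates of the bias in this trial. The change should be made, since data not collected cannot be restored later.

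**What to change.** 1. In the safety section, separate stopping study treatment from leaving the study. State that stopping treatment does not end outcome follow-up, and that these patients stay in MACE and bleeding follow-up at the scheduled visits to month 24 unless they withdraw consent. This reconciles the section with Follow-up and with the intention-to-treat statement. No clinical stopping rule is proposed or judged.
2. So that the promise on dropouts' data is met for the primary outcome, analyse first MACE with a clustered model that uses follow-up time. Options are a Cox model with hospital frailty, or a mixed model either with a complementary log-log link over visit intervals or with a person-time offset.
3. Keep a per-patient event mixed model with multiple imputation as a sensitivity analysis.

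The cost is wording in two sections, some extra contact with patients who are off treatment, and a little more analysis work. The visits are already scheduled.
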